## Abstract

Cervicogenic dizziness is dizziness triggered by movement or positioning of the cervical spine and is often accompanied by neck pain or stiffness. This is a prospective, pragmatic, assessor-blind, randomized controlled trial aimed at testing the efficacy and safety of adjuvant Chuna Manual Therapy (CMT) in patients with cervicogenic dizziness under usual care treatments. Fifty patients with cervicogenic dizziness will be randomly allocated to CMT or usual care (UC) groups in a 1 : 1 ratio. Extensive screening procedures, including examinations for central nervous system problems and nystagmus, will be applied to exclude other dizziness-inducing disorders. The eligible participants will receive 12 sessions of CMT plus UC or only UC over 6 weeks. CMT includes mandatory and discretionary techniques, whereas UC includes electrotherapy, thermotherapy, and patient education. The efficacy will be evaluated primarily as Dizziness Handicap Inventory score. The severity and frequency of dizziness, the level of neck pain or stiffness, and the cervical range of motion will also be evaluated. Safety will be assessed by adverse events. The data will be statistically analyzed at *p* < 0.05.* Trial Registration*. This trial was registered with Clinical Research Information Service (CRIS) in Korea, KCT0002565, on 29 November 2017, https://cris.nih.go.kr/cris/search/search_result_st01_kren.jsp?seq=9610<ype=&rtype=.

## 1. Introduction

Cervicogenic dizziness, also known as cervical dizziness, is dizziness originating from the cervical spine [1], in other words, symptoms of giddiness triggered by cervical movements or positions, possibly accompanied by neck pain or stiffness [2]. The prevalence of cervicogenic dizziness is unclear; however, it has been reported that 65 to 66% of dizziness in the elderly could be attributed to cervical spine dysfunction, including spondylosis [2, 3], which is a common [4] and increasingly prevalent [5] cause of dizziness.

The causes of cervicogenic dizziness are controversial [6]. A recent review suggested that Barré-Liéou syndrome, proprioceptive cervical vertigo, bow-hunter syndrome, and migraine could induce cervicogenic dizziness, but this has not yet been confirmed [3]. Another review suggested that whiplash-associated disorders or degenerative cervical disorders could be causes [4]. Because of this uncertainty, physicians usually diagnose cervicogenic dizziness by exclusion [7].

The treatment of cervicogenic dizziness has not yet been standardized. Physical therapies [3, 5, 8], surgery [3, 7], nonsteroidal anti-inflammatory drugs (NSAIDs) [9], trigger point injection with lidocaine [5], acupuncture therapy [9], and patient education [10], as well as miscellaneous manual therapies [2, 11–14], have been explored in previous studies for reducing the severity and frequency of dizziness and improving the cervical range of motion, but no definite conclusions have been reached.

Chuna Manual Therapy (CMT) is a spinal manipulation technique based on the traditional Korean medicine (TKM) theory that both function and structure have systematic correlations. It is a therapeutic technique for modulating both orthopedic and functional balances simultaneously [15]. CMT usually involves high-velocity and low-amplitude thrusts to the joints and applies manual force to joints in the passive range of motion [16]. It is widely used in clinical practice for patients with musculoskeletal pain, such as low back pain, neck pain, or temporomandibular joint disorders [15]. A few clinical studies conducted in China have shown the efficacy of CMT or similar manual therapies for cervicogenic dizziness or vertigo. CMT has been compared with nimodipine administration [17], traction therapy [18], or combined treatment with acupuncture [19, 20], using randomized or nonrandomized designs. However, most of these interventions were carried out using muscle or tissue massage, which are not the similar techniques to Korean CMT spinal manipulation. Moreover, most of these studies assessed efficacy using invalidated response measures. Given the overall low quality of the studies and the differences in CMT techniques, there remains a need to rigorously demonstrate a clinical effect of CMT on cervicogenic dizziness.

The objective of this randomized controlled trial (RCT) is to test the efficacy and safety of 6-week CMT in male or female subjects, aged between 20 and 70 years, with cervicogenic dizziness, and compare them with the results from usual care (UC).

## 2. Materials and Methods

The trial title is “Adjuvant Chuna Manual Therapy in Subjects with Cervicogenic Dizziness (CHERIE Study): A Study Protocol for a Prospective, Pragmatic, Assessor-Blind, Randomized Controlled Trial.” This study protocol was developed in accordance with the Standard Protocol Items: Recommendations for Interventional Trials (SPIRIT) 2013 statement [21]. Because there are no CMT-specific recommendations for trial design, we referred instead to the Revised Standards for Reporting Interventions in Clinical Trials of Acupuncture (STRICTA): extending the CONSORT statement [22]. The relevant SPIRIT checklist is attached as* supplementary data* (available here).

### 2.1. Objectives and Hypothesis

This study is aimed primarily at exploring the therapeutic effect of adjuvant CMT for 6 weeks in male and female patients (20–70 years old) with cervicogenic dizziness, previously under usual care treatments. The null hypothesis is that the mean Dizziness Handicap Inventory (DHI) scores at baseline and at week 6 will be equal for the CMT and UC groups.

Second, the severity and frequency of cervicogenic dizziness after CMT or UC will be evaluated, along with other outcome measures. Differences between the two groups in neck pain, stress level, and quality of life (QoL) will also be assessed. The safety of CMT will be examined using adverse event (AE) reporting.

### 2.2. Study Design

This study is a prospective, pragmatic, assessor-blind, randomized controlled trial. Fifty patients complaining of recurring dizziness with cervical origins, with DHI score ≥ 16 at baseline, will be randomly allocated to either the CMT or UC group, with a 1 : 1 ratio. After eligibility assessment and a 1-week run-in period, the participants will receive 12 sessions of CMT combined with UC, or UC only, over 6 weeks. CMT consists of mandatory and discretionary techniques, and skilled KMD doctors will perform the techniques considered to be optimal for each patient's condition. This latitude in treatment selection is why the study is designated as pragmatic. UC includes electrotherapy, thermotherapy, and patient education. A flowchart and timetable for the study are shown in Figure 1 and Table 1, respectively.

### 2.3. Setting and Recruitment

Two TKM hospitals will recruit eligible patients: the Kyung Hee University Korean Medicine Hospitals in Hoegi and Gangdong in Seoul, Republic of Korea. Participants will be recruited mainly from outpatient clinics. Recruiting advertisements will be posted on hospital web pages and noticeboards.

### 2.4. Ethical Review and Trial Registration

The study protocol (version 1.0) and informed consent form were peer-reviewed and approved by the Institutional Review Board of Kyung Hee University Korean Medicine Hospital on 11 August 2017 (KOMCIRB-170717-HR-026), in accordance with scientific and ethical regulations, that is, Good Clinical Practice and relevant laws of the Ministry of Food and Drug Safety in Korea. The trial was registered at CinicalTrials.gov on 19 September 2017 (NCT03291912, https://clinicaltrials.gov/show/NCT03291912). Personal information will not be collected and only encrypted code will be used for trial records.

### 2.5. Eligibility Criteria

The inclusion criteria are as follows:Men or women aged between 20 and 70 yearsNeck pain or stiffness with dizziness related to movement or positioning of the cervical spineRecurring symptoms of dizziness for 1 month or moreDHI ≥ 16 at baselineInformed consent for study participation

 The exclusion criteria are as follows:Dizziness induced by vestibular disorders (benign paroxysmal positional vertigo, peripheral vestibulopathy, Meniere disease, vestibular neuritis, etc.)Dizziness induced by central nervous system (CNS) disorders (cerebellar ataxia, cerebellar infarction/hemorrhage, demyelination, vertebrobasilar insufficiency, epilepsy, increased intracranial pressure, Parkinson's disease, migraine, etc.)Dizziness induced by cardiovascular disorders (arrhythmia, heart valve disease, anemia, orthostatic hypotension, coronary artery disease, etc.)Dizziness induced by active or uncontrolled disease (uncontrolled diabetes mellitus, hypertension, respiratory or endocrinological disorders, etc.)Drug-induced dizzinessSevere chronic or terminal diseases (malignant cancer, tuberculosis, etc.)Chronic psychiatric diseases under treatment (depression, panic disorder, etc.)Medical conditions for which CMT is forbidden (spinal tumor, acute fracture, infectious spondylopathy, congenital malformations of the spine, history of spinal operation within the past 3 months, progressive neurological damage, severe neurological symptoms, spinal fixation devices, syringomyelia, hydrocephaly, etc.)Treatment within the previous 1 week for cervicogenic dizziness (NSAIDs, steroid, herbal drug, acupuncture, manual therapy, etc.)Women with (suspected) pregnancy or breast-feedingSuspicion of alcohol or drug abuseParticipation in another clinical study within the previous 1 monthDifficulty in communicating with the investigatorsOther unanticipated reasons for ineligibility to participate

### 2.6. Dropout Criteria

Enrolled participants will be dropped if (a) the investigators detect ineligibility after random allocation, (b) participants withdraw consent for participation, refuse to receive CMT or UC, or are lost to follow-up, (c) serious adverse events or complications that need treatment are reported, or (d) the participants or investigators significantly violate the study protocol, including the criteria concerning concomitant medication.

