### 2.7. Randomization, Allocation, and Blinding

Random number sequences will be generated by an independent statistician ([name]) using SAS® 9.4 software (SAS Institute Inc., Cary, NC). The randomization will be block-stratified by the recruitment hospital to keep the numbers of each group similar throughout the study. The statistician will provide each hospital with sealed envelopes, in each of which a random number and an allocated group are written. Immediately after a participant is found to be eligible according to the screening process, a TKM doctor who will administer UC or CMT will open the next envelope in the sequence. Because this study is open-labeled to the investigators and patients, only the outcome assessors will be blinded. The outcome assessors will be TKM doctors different from those who administer CMT and UC. Only clinical emergency situations will allow breaking of the randomization code and blinding. At the end of the study, each outcome assessor will be asked which group he or she thought the patient was allocated to, and the answers will be used to calculate a blinding index (BI) [23].

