### 2.10. Concomitant Medications

Drug administration (betahistine, difenidol, flunarizine, cinnarizine, dimenhydrinate, ginko, meclizine, metoclopramide, scopolamine, pentoxifylline, perphenazine, ergoloid mesylate, droperidol, phenobarbital, prochlorperazine, promethazine, trimethobenzamide, vertigoheel, NSAIDs, steroids, etc.), herbal remedies, manual therapies, any type of acupuncture, moxibustion, or cupping, to relieve dizziness, back pain, or stiffness, will be forbidden throughout the study.

Any signs of the use of drugs that can induce dizziness will be monitored closely during every visit.

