### 2.15. Sample Size Calculation

RCTs evaluating the efficacy of a manual therapy, compared with placebo, for cervicogenic dizziness gave values for the mean changes and standard deviations [11, 13]. With 15.9 as the mean difference between the intervention and control groups and 12.91 as the standard deviation, the necessary sample size calculated using PASS 14 was 12 per group (two-sided, *α* = 0.05 and 1 − *β* = 0.9). We will allocate a total of 50 participants (25 per group), allowing for an anticipated drop-out rate of 40%.

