### 2.16. Statistical Analysis

The full analysis set is defined as the group of participants who received CMT or UC and were assessed for the primary outcome at least once. The “per protocol” set is defined as the group of participants who completed all planned interventions and outcome assessments. Efficacy data will be analyzed primarily using the full analysis set and secondarily using the per protocol set. The missing data will be imputed using the “last observation carried forward” method. Safety data will be analyzed using the safety assessment set, which is defined as the group of participants who received CMT or UC at least once.

The primary and secondary outcomes will be statistically analyzed using two-sample *t*-tests or Wilcoxon's rank-sum tests for intergroup comparisons and paired *t*-tests or Wilcoxon's signed-rank tests for intragroup comparisons. Categorical variables from demographic data or AEs will be analyzed using the Chi-square test or Fisher's exact test.

An independent statistician ([name]) will analyze the data at *p* < 0.05 with SAS 9.4 software (SAS Institute Inc.).

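### The dropout rule treats stopping treatment as leaving the study, so obtainable week-3 and week-6 DHI scores will probably go unobserved, possibly in a way that depends on arm and response

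*Protocol article*

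**What the plan says.** Section 2.6 (Dropout Criteria) gives four grounds with a single consequence, that the enrolled participant is dropped:

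- (a) ineligibility discovered after allocation;
- (b) "participants withdraw consent for participation, refuse to receive CMT or UC, or are lost to follow-up";
- (c) a report of a serious adverse event, or of a complication for which treatment is required;
- (d) "the participants or investigators significantly violate the study protocol, including the criteria concerning concomitant medication".

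Other sections bear on what this does:

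- Section 2.10 bans a list of drugs, herbal remedies, manual therapies, acupuncture and related treatments: when used "to relieve dizziness, back pain, or stiffness, will be forbidden throughout the study".
- Section 2.7 states: "Because this study is open-labeled to the investigators and patients, only the outcome assessors will be blinded".
- Section 2.15 sets 25 per group, "allowing for an anticipated drop-out rate of 40"%.
- Section 2.16 bases the primary efficacy analysis on a full analysis set of participants "who received CMT or UC and were assessed for the primary outcome at least once", and fills missing values by last observation carried forward (LOCF). The secondary per-protocol set contains only those who finished every intervention and assessment.
- Table 1 schedules the DHI at screening, day 0, V7 (week 3) and V13 (week 6).

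The article does not say whether a dropped participant is still assessed at week 3 or week 6.

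**The concern.** Withdrawn consent and true loss to follow-up cannot be prevented. The other grounds are different. A patient who refuses further sessions, takes a forbidden drug, has a complication, or is treated by an investigator who breaks the protocol can usually still fill in a questionnaire. Section 2.6 puts both kinds of event under one rule, so endpoint data that could be had may never be collected.

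The avoidable losses are unlikely to be a random sample:

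- The forbidden treatments are those taken for the symptoms, so patients who remain dizzy or stiff are the likeliest to trigger ground (d).
- Patients and treating doctors know the arm. Refusing treatment, and judging whether a violation is significant, can both depend on it.

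At stake is a week-6 comparison in which part of the primary endpoint is imputed for reasons that may be tied to arm and response. Data never collected cannot be recovered at the analysis stage.

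**Working it through.** **1. The plan's own figures (section 2.15).** Inputs: difference 15.9, SD 12.91, two-sided 0.05, power 0.90, 25 per group, 40% dropout.

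- Patients without an observed endpoint: 50 × 0.40 = 20.
- Patients left per group: 25 × (1 − 0.40) = 15.
- The stated 12 per group does not lead to 25, since 12 / (1 − 0.40) = 20, whereas 15 / (1 − 0.40) = 25. A two-sample t-test needs 15 per group for 90% power; 12 gives 82.2%. That mismatch is a separate matter. What matters here is that the allowance treats a dropout as a lost endpoint, which supports reading dropped as no longer assessed.

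**2. What replaces the missing score.** From the Table 1 schedule:

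- Dropped before V7: the day-0 score is carried forward, so the change is 0.
- Dropped after V7: the week-3 score is carried forward, so the week-6 change equals the week-3 change.
- Never treated: excluded from the full analysis set.

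For the treated patients, write p for the proportion dropped in an arm and m for the mean, among those dropped, of the carried-forward change minus the change that would have been observed. Then

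bias = p(CMT) × m(CMT) − p(UC) × m(UC).

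The article gives none of these four quantities. The 40% is not split by cause or by arm.

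**3. Illustration.** Assumptions, not from the documents except the SD and group size: no true difference; mean DHI change −5 at week 3 and −10 at week 6 in both arms; SD 12.91; correlation 0.5; 25 per group; patients doing worse at week 6 more likely to be dropped. There were 10,000 simulated trials per row. A negative bias favours the arm with more drops.

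| Dropped (arm 1 / arm 2) | Handling of dropped patients | Bias, DHI points | Type I error |
|---|---|---|---|
| 40% / 10% | still assessed at week 6 | 0.0 | 5.2% |
| 40% / 10% | week 3 carried forward | +0.6 | 4.7% |
| 40% / 10% | baseline carried forward | +1.1 | 5.2% |
| 40% / 10% | week 3 carried forward, week-3 mean −10 | −1.0 | 6.5% |
| 40% / 10% | week 3 carried forward, week-3 mean 0 | +2.1 | 6.4% |
| 40% / 10% | completers only | −4.1 | 20.1% |
| 30% / 20% | completers only | −1.3 | 10.3% |

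Under LOCF the sign changes with the assumed time course. The completers-only rows correspond to the per-protocol set. Continued assessment removes the bias.

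**4. Information.** For a t-test on the plan's own difference and SD, the noncentrality is (15.9 / 12.91) × √(n/2).

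- n = 15: 1.232 × 2.739 = 3.37, power 90.2%.
- n = 25: 1.232 × 3.536 = 4.35, power 98.9%.

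These compare 15 observed endpoints per group with 25, and ignore any dilution of the effect by non-adherence.

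**The case against.** The case against a stronger reading is substantial, and most of it stands.

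- A reader might infer that dropped patients are discarded from the primary analysis. They are not. Anyone treated with at least one DHI stays in the full analysis set, and because the DHI is taken at screening and day 0, nearly every treated patient qualifies on the stated wording. Only randomised patients who never start are left out, and nothing suggests that they are many. Full selection applies only to the per-protocol set, which is secondary.
- A reader might infer that any adverse event or deviation leads to dropping. Ground (c) is limited to serious events or complications needing treatment, and ground (d) to significant violations. The reactions that section 2.14 expects after CMT are described there as mostly mild and short-lived, so they would not normally trigger (c).
- Section 2.6 does not say that assessment stops. Section 2.4 refers to a protocol version 1.0 that is not shown and may cover follow-up after discontinuation. Non-collection is the natural reading, not an explicit statement.
- Using scores obtained after forbidden treatment answers a different question from the effect without such treatment, and section 2.2 ties the word pragmatic to freedom in choosing techniques. That is a legitimate choice of question. It is no reason to leave the scores uncollected, since collecting them keeps both analyses possible.

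What the objection does not remove is that one rule covers both avoidable and unavoidable loss, and that LOCF replaces an outcome that could have been observed.

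**Conclusion.** The point holds in a limited form. Followed as written, section 2.6 probably loses week-3 and week-6 DHI scores that could have been obtained, for reasons that may depend on arm and response. The primary analysis then rests on carried-forward values for those patients and omits randomised patients who never start.

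The size and direction of the bias cannot be derived from the article. A reader might multiply the planned 40% by an assumed 10-point difference between arms in the imputation error and obtain 0.40 × 10 = 4 points, a quarter of the planned 15.9. The documents do not support that figure. It charges the whole allowance to this rule, although the allowance must also cover withdrawn consent and loss to follow-up, and the 10 points have no source. In the simulations above, LOCF gave from about 1 point in favour of the arm with more drops to about 2 points against it, with type I error of about 5% to 6.5%. About 4 points and 20% arose only in a completers-only analysis with 40% against 10% dropped.

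The link to arm and response is an inference from the dropout grounds, the open label and the list of forbidden treatments; no rates by arm are given. Any separate criticism of LOCF would concern the same imputation bias, which should not be counted twice. The correction is worth making because it is cheap and cannot be made after the fact.

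**What to change.** - **Section 2.6:** separate discontinuing allocated treatment from withdrawing from the study. State that the DHI and the other patient-rated scales are collected at weeks 3 and 6 from every randomised patient who has not withdrawn consent to data collection, by phone or post if a visit is not possible, and that the deviation or medication is recorded.
- **Section 2.16:** define the primary set as all randomised patients, analysed in the arm to which they were allocated, and keep the per-protocol set as secondary.
- The clinical rules for stopping treatment stay as they are.

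The cost is a change of wording and a few extra questionnaires at time points already scheduled. The downside is that the estimated effect will include non-adherence and use of other treatments, and the trial report should say so. Patients who withdraw consent or cannot be reached will still have missing scores.

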### 2.7. Randomization, Allocation, and Blinding

Random number sequences will be generated by an independent statistician ([name]) using SAS® 9.4 software (SAS Institute Inc., Cary, NC). The randomization will be block-stratified by the recruitment hospital to keep the numbers of each group similar throughout the study. The statistician will provide each hospital with sealed envelopes, in each of which a random number and an allocated group are written. Immediately after a participant is found to be eligible according to the screening process, a TKM doctor who will administer UC or CMT will open the next envelope in the sequence. Because this study is open-labeled to the investigators and patients, only the outcome assessors will be blinded. The outcome assessors will be TKM doctors different from those who administer CMT and UC. Only clinical emergency situations will allow breaking of the randomization code and blinding. At the end of the study, each outcome assessor will be asked which group he or she thought the patient was allocated to, and the answers will be used to calculate a blinding index (BI) [23].

